### Statistical analysis

Descriptive statistics will be used to describe the characteristics of the sample. Linear regression will be used for the evaluation of continuous outcomes and logistic regression for dichotomized outcomes. Research condition (i.e. intervention or control group), will be entered in the model as the independent variable. Where relevant, models will be corrected for the baseline measurements (data of baseline questionnaire) and for potential confounders (age of child and parent, educational level of parents and ethnic background). Additionally, moderation of intervention effects by sociodemographic characteristics (educational level, income and ethnic background) is explored by adding an interaction term to the regression model.

Missing data on the questionnaires will be handled according to the questionnaire protocol.

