### Procedure

An opportunity sample of two preventive Youth Health Care centers (CJG Rijnmond and Rivas Zorggroep) in two regions of the Netherlands participated in this study.

Nineteen of the 27 care teams of the Youth Health Care center CJG Rijnmond participated as intervention group. These locations offer the intervention Supportive Parenting to parents at risk of parenting problems as part of their regular youth health care.

The care team in the area Goerree-Overflakkee of CJG Rijnmond and all 19 preventive Youth Health Care teams of Rivas Zorggroep participated as control group. At these teams, regular youth health care is offered, the intervention Supportive Parenting is not part of this regular care. Regular care consists of the regular well-child visits at set ages.

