### Power of the study

Two Youth Health Care centers participate in the study. Their teams invited 313 parents (for the intervention group) and 2346 parents (for the control group). Taking into account informed consent by 50 % and eligibility of 10 % to participate in the study for the control group, we expect data of 157 parents in the intervention group and 117 parents in the control group.

With the use of continuous measures and assuming a standard deviation of 1.00 in both groups, a power of 0.80 and an alpha of 0.05, these group sizes are sufficient to demonstrate a significant difference of 0.35 between the intervention group and the control group. This is appropriate to indicate relevant effects [31, 32].

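### Arm is set by care team (19 intervention, 20 control), but the regression models and the detectable difference of 0.35 treat parents as independent; the loss depends on an intra-team correlation that the article does not give

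*Protocol article*

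**What the plan says.** The Procedure section assigns whole teams to arms. On the intervention side, "Nineteen of the 27 care teams of the Youth Health Care center CJG Rijnmond participated as intervention group", and "These locations offer the intervention Supportive Parenting to parents at risk of parenting problems as part of their regular youth health care". On the control side stand "The care team in the area Goerree-Overflakkee of CJG Rijnmond" and "all 19 preventive Youth Health Care teams of Rivas Zorggroep participated as control group". That makes 19 intervention and 20 control teams, 39 in all, each wholly in one arm. A parent's arm follows from the team she belongs to.

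The Statistical analysis section says: "Linear regression will be used for the evaluation of continuous outcomes and logistic regression for dichotomized outcomes". Condition is the independent variable. Adjustment, where applicable, is for baseline scores, the ages of child and parent, education and ethnic background. No team, nurse or organisation term appears, and neither does a random effect or a robust variance.

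The Power of the study section expects 157 and 117 parents, assumes SD 1.00, power 0.80 and alpha 0.05, and concludes that "these group sizes are sufficient to demonstrate a significant difference of 0.35 between the intervention group and the control group". It gives no number of teams, ICC or design effect.

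**The concern.** Parents served by the same team share staff, working habits and a catchment area, so their outcomes may be correlated. Because arm does not vary within a team, variation between teams goes straight into the between-arm comparison. Ordinary regression does not count it. The intervals are then too narrow, and a nominal 5% test rejects a true null hypothesis more often than 5% of the time.

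The article itself gives reason to expect some correlation at provider level. Its objective includes relating nurse characteristics to the intervention's effects, and it measures nurse personality, burnout and the parent–nurse working alliance.

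The point applies to every primary between-group comparison. It is not a detail left to an analysis plan, because the article states both the model and a power figure.

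**Working it through.** **Inputs from the article.** Expected parents: 157 intervention, 117 control. Teams: 19 and 1 + 19 = 20. SD 1.00, power 0.80, alpha 0.05; sidedness is not stated.

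**Group sizes.** The article assumes "informed consent by 50 % and eligibility of 10 % to participate in the study for the control group". With 313 and 2346 parents invited, 313 × 0.5 = 156.5 and 2346 × 0.5 × 0.1 = 117.3. These match 157 and 117.

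**The plan's own figure.** For independent parents, two-sided, the minimum detectable difference (MDD) is

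MDD = (1.960 + 0.842) × √(1/157 + 1/117) = 0.342

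Power at a difference of 0.35 is 0.817. A one-sided test would give 0.304 and 0.889, so the stated 0.35 fits a two-sided calculation with independent observations. No hidden allowance for clustering fits within it.

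**Adding team.** Assume equal team sizes within each arm: m₁ = 157/19 = 8.26 and m₂ = 117/20 = 5.85. Then:

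- design effect in each arm: DE = 1 + (m − 1) × ICC
- SE = √(DE₁/157 + DE₂/117), and SE₀ is the same with both DE = 1
- MDD = (1.960 + 0.842) × SE
- power at 0.35 = Φ(0.35/SE − 1.960)
- actual type I error of the unadjusted-for-team test = 2 × [1 − Φ(1.960 × SE₀/SE)]

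Example at ICC 0.05: DE₁ = 1 + 7.26 × 0.05 = 1.363 and DE₂ = 1 + 4.85 × 0.05 = 1.242. SE = √(1.363/157 + 1.242/117) = 0.139, against SE₀ = 0.122. MDD = 2.802 × 0.139 = 0.389.

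The ICC is an assumption throughout:

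| ICC | DE intervention / control | SE ÷ SE₀ | MDD | Power at 0.35 | Type I error |
|---|---|---|---|---|---|
| 0 | 1.00 / 1.00 | 1.00 | 0.342 | 81.7% | 5.0% |
| 0.01 | 1.07 / 1.05 | 1.03 | 0.352 | 79.5% | 5.7% |
| 0.02 | 1.15 / 1.10 | 1.06 | 0.362 | 77% | 6.4% |
| 0.05 | 1.36 / 1.24 | 1.14 | 0.389 | 71% | 8.5% |
| 0.10 | 1.73 / 1.49 | 1.26 | 0.431 | 62% | 12.0% |

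**Where the stated figure stops holding.** The MDD passes 0.350 at an ICC of about 0.008 and no longer rounds to 0.35 above about 0.013.

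**Sensitivity.** Unequal team sizes make it worse. With an assumed coefficient of variation of 0.5 and ICC 0.05, the MDD is 0.402, power 68% and type I error 9.5%. Using a t distribution on 39 − 2 = 37 degrees of freedom in place of the normal lowers power by about two percentage points, for example from 71% to 69% at ICC 0.05 with equal team sizes.

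**The case against.** A reader might infer that the standard errors are certainly too small and that 0.35 is certainly not delivered at 80% power. The documents do not support that. They give no ICC, and nothing in them shows which value is realistic. At ICC 0.01 power is 79.5%, which is no practical loss. With about six to eight parents per team, the inflation is modest at low ICC.

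The table also describes an unadjusted comparison, whereas the planned models adjust for covariates. What counts is the correlation left after adjustment, and education and ethnic background may absorb part of any difference between areas. Baseline adjustment may also recover precision. If variance scales by 1 − r² (an assumption), 80% power at 0.35 returns with r of about 0.26 at ICC 0.02 and about 0.44 at ICC 0.05. This stands, with limits. The power section does not claim that gain, and a smaller residual variance does not by itself correct the type I error. The parenting subscales of the two family questionnaires were left out at baseline. The child behaviour checklist starts at age 1½, so it cannot have a baseline value at 1–3 months.

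Two further points stand. That one nurse serves several study families is an inference, since no caseload or number of nurses is given, and a nurse level may not be estimable. A team-level model also leaves arm almost wholly aligned with organisation: in 38 of the 39 teams, arm follows the organisation. Correct team-level standard errors would therefore not by themselves secure a 5% error rate for an intervention effect. Neither point justifies standard errors that ignore team.

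**Conclusion.** The point holds in conditional form. The stated models and the stated detectable difference both ignore the unit that determines arm, and 0.35 holds only if parents are independent. With any positive within-team correlation remaining after adjustment, standard errors are understated and the error is towards false positives.

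The size is not known from the article. Over an assumed ICC of 0.01 to 0.10, with equal team sizes within each arm and no covariate adjustment, the detectable difference runs from 0.352 to 0.431, power at 0.35 from 79.5% to 62%, and type I error from 5.7% to 12.0%. The lower end is negligible. From about 0.02 upwards, the stated figure is missed unless baseline adjustment makes up the difference. The table illustrates the sensitivity to clustering and does not give the actual error rates of the planned adjusted models.

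**What to change.** - **Analysis.** Fit the planned linear and logistic models with a random intercept for care team and small-sample degrees of freedom, or keep the regressions and use cluster-robust standard errors with a small-sample correction. With 39 teams either is feasible. Fix the choice before the outcome data are analysed.
- **Nurse.** Include nurse only as a sensitivity analysis, where it is recorded and estimable.
- **Power statement.** Replace the single 0.35 with a detectable difference conditional on an assumed ICC, for example about 0.36 to 0.39 at ICC 0.02 to 0.05. Do not enrol more parents. The restatement changes no recruitment decision, but it tells readers what the fixed sample can show.
- **Limitation to state.** Say that team-level modelling does not separate arm from organisation, because only one control team comes from the intervention organisation.

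The cost is somewhat wider intervals, revised wording and one restated planning figure. Team must be on record for each parent. This is plausible, because arm follows from team, but the article does not say so and it should be confirmed.

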### Interviews and focus group interviews

Additionally, interviews [one-on-one] and focus group interviews [with multiple respondents] with Youth Health Care nurses and parents are performed to investigate the factors that promote and/or hinder a wider implementation of the intervention Supportive Parenting. The interviews and focus group interviews will be semi-structured [33] and focus on which aspects of the intervention Supportive Parenting parents and Youth Health Care nurses appreciate, which aspects should be further improved, and the perceived effect of the intervention Supportive Parenting on parents’ empowerment. Furthermore, Youth Health Care nurses will discuss opportunities and obstacles for wider implementation of the intervention Supportive Parenting (e.g. among parents of different subgroups, older children).

#### Participants

##### Interviews and focus group interviews with parents

Parent(s)/caregiver(s) participating in the intervention group of the controlled trial, who are finishing or have already finished the intervention Supportive Parenting are invited by email to participate in an interview or focus group interview. In addition, Youth Health Care nurses who provide the intervention invited parents who are not part of the intervention group but are finishing or have already finished the intervention Supportive Parenting to participate in the interviews.

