The intervention Supportive Parenting consists of six 90 min home visits during the first 18 months after childbirth and focuses on the following elements of parental empowerment: activating social networks, increasing parenting skills and supporting parent(s)/caregiver(s) in getting grip on their own life. A preventive Youth Health Care nurse provides the six home visits of approximately 90 min each. There is one home visit every three months, but according to parents’ needs and preferences there can be more visits during the first months after birth or more visits at the end of the intervention. A home visit consists of a fixed part and a flexible part. During the fixed part the following topics are discussed: handling of/coping with developmental history of the parents, experience of parenthood, expectations with respect to the development of the child, social support and professional support for the family. Additionally during every visit information is given about the different developmental stages of children and the corresponding specific parenting tasks. The flexible part is client-centered. Empowering experiences as well as worrisome experiences are addressed. Parents are asked to come up with ways to improve worrisome aspects of their family-life. The topics of the flexible part are chosen by the parent(s)/caregiver(s) [19]. The intervention is voluntary and parents can indicate to the Youth Health Care nurse if they would like to discontinue the intervention.

The Youth Health Care nurses who provide the home visits have a vast experience in Youth Health Care and have received additional training for the intervention Supportive Parenting. The nurses have the necessary knowledge to provide parent(s)/caregiver(s) with information about health- and development-related issues. However, the nurses are not equipped to provide psychotherapeutic treatment or family therapy and therefore refer to more extensive treatment if deemed necessary [19].

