#### Other measures

Parent characteristics that are assessed include various demographic factors (age, country of birth, income in euros, educational level, employment situation, and family structure). Additionally, the intervention group completes questions on the amount of home visits they have received, and their satisfaction with the intervention, to check for adherence to intervention protocols. Each questionnaire contains an open space for parents to write down comments and questions with regard to the study and the intervention.

Professional characteristics that are assessed are personality, measured by the Brief HEXACO Inventory [26] and work-related factors, measured by the Utrechtse Burnout Scale [27]. Both the Youth Health Care nurse and parents complete the Working Alliance Inventory (in Dutch: Werkalliantie Vragenlijst [WAV]) to assess the quality of the relation between parent and nurse [28].

Child characteristics which are assessed are gender, preterm, low birthweight and temperament. Temperament of the child is measured by an adapted version of six scales of the Infant Behavior Questionnaire – Revised (IBQ-R) [29] as used in a study by Roza et al. [29]. The IBQ-R asks parents to rate the frequency of specific behaviors observed during the past week. The adapted version of the IBQ-R uses six of the 14 scales because these scales are judged by Roza et al. [30] to be the most important for the later prediction of the most prevalent behavioral problems in children (e.g. anxiety, aggressive behavior and attention problems). The six scales in the adapted version include Activity Level, Distress to Limitations, Fear, Duration of Orienting, Recovery from Distress and Sadness. Based on the results of the pilot study carried out by Roza et al. [30], the original 7-point scale was adapted to a 3-point scale with 0 = *never present*, 1 = *sometimes present* and 2 = *often present.* This was done, because respondents rarely used the extreme points of scales. Higher scores on the scales, except on the Falling Reactivity scale, indicate more difficult behavior. The scores for each scale were calculated by dividing the sum of the items by the number of completed items [30].

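### Both parent interview routes are limited to those finishing or having finished the programme, so the interviews cannot hear directly from parents who discontinued

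*Protocol article*

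**What the plan says.** The section on interviews and focus group interviews gives their purpose: with nurses and parents, "to investigate the factors that promote and/or hinder a wider implementation of the intervention Supportive Parenting". Both groups are to discuss what they value in the programme, what should be improved, and its perceived effect on empowerment. Nurses are additionally to discuss opportunities and obstacles for wider use. The Objective section lists the same implementation question among the aims of the study.

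The section on interviews with parents gives two ways in. Intervention-group parents "who are finishing or have already finished the intervention Supportive Parenting are invited by email". In addition, nurses who deliver the programme "invited parents who are not part of the intervention group but are finishing or have already finished the intervention Supportive Parenting". No other parent route is described.

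The section describing the intervention states: "The intervention is voluntary and parents can indicate to the Youth Health Care nurse if they would like to discontinue the intervention".

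The section on other measures describes further sources of information. "Each questionnaire contains an open space for parents to write down comments and questions with regard to the study and the intervention", and "the intervention group completes questions on the amount of home visits they have received, and their satisfaction with the intervention".

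**The concern.** The condition for being interviewed is reaching, or nearly reaching, the end of the programme. One purpose of the interviews is to learn what hinders implementation and what should be improved. Parents who gave up part-way have first-hand experience of at least some of what hinders, and their views on improvement and perceived effect may differ from those of parents who stayed. The article foresees that some will stop, then gives both parent routes an entry condition that leaves them out.

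This is a stated eligibility rule that works against a stated aim, not a detail that a condensed article has left to a fuller document. At stake is how far the parent interviews can be read as the views of parents offered the programme, as opposed to parents who saw it through.

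**Working it through.** The point is mainly one of reading, so the relevant statements are set side by side.

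1. **Aim.** The opening sentence on the interviews covers both nurses and parents, and includes factors that hinder. The parent topics include improvement and perceived effect.
2. **Route 1, trial parents.** Entry requires finishing or having finished.
3. **Route 2, parents outside the trial.** Entry requires the same.
4. **Stopping early.** This is foreseen: parents may tell the nurse that they wish to discontinue.
5. **Result.** On a plain reading of 2 and 3, a parent in the group described in 4 has no route to an interview. This follows from the wording and needs no assumed rate.

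**Could "finished" include ending early?** The article does not define finishing as six visits received, and visit timing is flexible, so the word could be stretched. But the intervention section has its own word, discontinue, for stopping. If the wider meaning is intended, the text should say so.

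**Do other channels fill the gap?**
- *Open comment space.* It is in every questionnaire and is not restricted to finishers. It reaches only stoppers who return a questionnaire and choose to write about stopping.
- *Visit count and satisfaction.* These are asked of the intervention group as a whole. They show how much was received and how it was liked. The article describes no item on reasons for stopping.
- *Nurse interviews.* Nurses hear from parents who want to stop and can pass on reasons. That account is second-hand, and a parent may not tell the nurse a reason that concerns the nurse.

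Each channel gives something. None is a semi-structured conversation with the parent about improvement and perceived effect.

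**How many parents?** The article gives no discontinuation rate. Its expected intervention group is 313 × 0.50 = 156.5, stated as 157, which reproduces. If, purely as an assumption, 20% to 40% of these stopped, the parents without an interview route would number 0.20 × 157 = 31.4 to 0.40 × 157 = 62.8, about 31 to 63. The range has no basis in the document. It shows only how the count scales with the rate, and it does not measure bias in the findings.

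**The case against.** The case on the other side has real force on several points.

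- **Parents who stop can still be heard.** A reader might infer that they can never say why they stopped. The documents do not support that: the comment space, the satisfaction questions and the nurse interviews are all open to such information. This stands, and it limits the point to direct interviews.
- **Wider implementation is illustrated mainly as extension to other groups**, such as parents of older children, pregnant women and different ethnic groups, and obstacles are assigned explicitly to nurses. This also stands: reasons for stopping are part of the question, not the whole of it. But the opening sentence puts hindering factors to parents too, and improvement and perceived effect are topics for them.
- **Finishing does not imply satisfaction.** A reader might infer that both routes pick satisfied parents and that the conclusions will be too favourable. This is plausible, but the article does not say it, and finishers are asked what should be improved. Nor does it say that nurses choose among eligible parents; it says only that they invite them.
- **Qualitative samples are purposive and need not be representative.** Parents at or past the end are well placed to judge the whole programme. That justifies including them; it does not justify excluding everyone else when barriers are among the topics.
- **The article states openly who is interviewed and promises only relevant insights.** True, but it does not limit those insights to completers.

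**Conclusion.** The point holds in a limited form. As written, both parent routes select on finishing or having finished, so the interviews cannot hear directly from parents who discontinued, although stopping is foreseen and hindering factors, improvements and perceived effect are what the interviews are for. The other channels reduce the gap without closing it.

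The conclusion rests on the ordinary meaning of finishing, as distinct from discontinuing, and on the two routes being the only ones. The size and direction of any bias are unknown because no stopping rate is given and nothing shows how stoppers' views would differ.

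A reader might extend the point to the trial's main results. The documents do not support that: the hypotheses, primary outcomes, power calculation and regression analyses do not draw on the interviews. This is a modest but worthwhile correction to the qualitative component.

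**What to change.** Send the e-mail invitation already planned to all intervention-group parents, including those who discontinued. State what counts as finishing and as discontinuing, and report the two groups separately, using the visit count that the intervention group already provides. Because visit timing is flexible, the definition should be written down before the interviews are analysed.

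The cost is a longer mailing list and a few more interviews, with no new instrument. Response from discontinuers is likely to be low, so the number invited and interviewed in each group should be given.

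If the interviews are too far advanced for this, state in the report that the parent findings represent completers' views only, and describe what the questionnaires and nurses contributed about parents who stopped as indirect evidence.
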